| Contraceptive method history:                 | Please indicate which, if any, methods of birth control you used right before this pregnancy. Say yes to all that apply. | BL |  Birth control pills
 Male Condom
 Partner's vasectomy
 Tubal sterilization
 Withdrawal or pulling out
 Contraceptive injection (Depo-Provera)
 Hormonal implant (Nexplanon)
 Natural family planning/rhythm method
 Female condom
 Sponge, diaphragm, or cervical cap
 Emergency contraception
 Spermicides
 Intrauterine device (IUD)
 Contraceptive patch
 Vaginal contraceptive ring/ Nuva Ring
 Other ( Specify ):
<hr/>  None
 Don't know or unsure |                                                                                                                                                                                                                                                                                                                        |
| In-person or virtual delivery of the Decision | [noted by research assistant at UT site, where virtual and in-person recruitment is being used]                   | BL | Dichotomous (in-person/virtual)                                                                                                                                                                                                                                                                                                                                                                                                                                                                                                                                                                                                                                                                                                                                                                                                                                                                                                                                     | Dichotomous (in-person/virtual)                                                                                                                                                                                                                                                                                        |

|                              |                                                                                                                                                                                                    |                         |                               |                               |
|------------------------------|----------------------------------------------------------------------------------------------------------------------------------------------------------------------------------------------------|-------------------------|-------------------------------|-------------------------------|
| Aid                          |                                                                                                                                                                                                    |                         |                               |                               |
| Language of the decision aid | [must be noted in the dataset manually; it is determined by which Decision Aid variables are completed by the participant--Spanish version pulls different variables from the Decision Aid] | Within the Decision Aid | Dichotomous [English/Spanish] | Dichotomous [English/Spanish] |

†Consent for sterilization - hhs.gov. <https://opa.hhs.gov/sites/default/files/2020-07/consent-for-sterilization-english-updated.pdf>. Accessed August 11, 2022.

‡ Defining adult overweight & obesity. Centers for Disease Control and Prevention. <https://www.cdc.gov/obesity/basics/adult-defining.html>. Published June 3, 2022. Accessed August 11, 2022.

## Statistical Analyses

### Descriptive and Baseline Statistics

All primary and secondary outcomes will be described using sample means or proportions along with accompanying confidence intervals. Suitable transformations will be considered for continuous variables if there are substantial departures from normality. Baseline characteristics will be compared between the study arms using two-sample t-tests or chi-square tests, as appropriate (see Outcome Variables tables above).

### Primary and Secondary Hypotheses

For the following primary and secondary hypotheses, we will conduct an intention-to-treat analysis using linear or logistic regression to test intervention effects controlling for study site. The beta coefficient and corresponding 97.5% confidence interval will be used to assess the effect of the intervention.

- **Primary Hypothesis a:** Compared to women who receive usual care alone, women randomized to the decision aid arm will have greater knowledge about sterilization and alternative options at T1
- **Primary Hypothesis b:** Compared to women who receive usual care alone, women randomized to the decision aid arm will have lower decisional conflict in postpartum contraceptive choice at T1
- **Secondary Hypothesis a:** Compared to women who receive usual care alone, women randomized to the decision aid arm will also be less likely to select sterilization and more likely to select an alternative method at T1
- **Secondary Hypothesis b:** Compared to women who receive usual care alone, women randomized to the decision aid arm will also be more satisfied with their decision at 3-month follow-up (T3)

### Handling Missing Data

We will record reasons for dropout at T2 and T3 and investigate any relationship with study arm. We will also compare baseline characteristics between women who do and do not complete the study. With regard to missing data, we will investigate the mechanism and degree of missingness using established techniques. If the amount of missingness is great, we will compare various imputation techniques to determine how robust the overall inferences are.

### Exploratory Hypotheses

For the following exploratory hypotheses, regression will be used to test intervention effects controlling for study site. The beta coefficient and corresponding 97.5% confidence interval will be used to assess the effect of the intervention.

- **Pre- and Post-Dobbs SCOTUS Decision Exploratory Analyses:** regression analyses are adjusted for study site  
\*\*note state interaction effects below\*\*
  - Date for the *Dobbs* decision can be categorized in 3 ways:
    - Dichotomized as before June 24, 2022 and June 24, 2022 or later (the verdict)
    - Dichotomized as before May 1, 2022 and May 1, 2022 or later (the leak)
    - Categorical: before May 1; May 1- June 23; June 23 or later (would measure effect of the leaked news and then effect of the full impact)
  - How did the *Dobbs* SCOTUS decision impact recruitment?
    - Recruitment changes pre- and post-Dobbs
      - More interest in joining study
      - Differences in recruitment across gravida and parity
  - How has it affected our outcomes of interest?
    - The desire for sterilization at baseline
    - Decisional conflict about contraceptive method selection at T1 predicted by date
    - Ease in contraceptive decision making at T1 and T2 predicted by date
    - Certainty about sterilization decision at T1 and T2 predicted by date
    - Contraceptive method selected at T1 and T2 predicted by date
    - Contraceptive method used at T3 predicted by date

- **\*\*Interaction effect between date and state on all outcomes (for every outcome)\*\***

- **Additional Sensitivity Analyses for Primary and Secondary Outcomes**

- We will run additional sensitivity analyses to test robustness of the intervention effects after adjusting for any significant differences in baseline characteristics (to be identified during analysis) between the intervention and control group that are also associated with the outcomes of interest:
  - 1) sterilization knowledge at T1
  - 2) decisional conflict at T1
  - 3) contraceptive method selected at T1
  - 4) satisfaction with decision-making at T3
- We will run additional sensitivity analyses to test robustness of the intervention effects after adjusting for differences in:
  - T3 Outcomes (satisfaction with decision-making at T3):
    - Provider sterilization counseling between T1 and T3 (composite variable of this question at T3 about counseling during this pregnancy isolating those who said they already received this counseling prior to or during this pregnancy at baseline)
    - Provider contraceptive counseling between T1 and T3
    - Medicaid consent signed between T1 and T3
    - Provider sterilization and/or Medicaid consent between T1 and T3

- **Subgroup Analyses (Interactions, no *a priori* hypothesis, not powered) of the Primary Outcomes by:**

*Regression model needs to control for site, including direct effects of the decision aid and the variable of interest below. Check for collinearity (VIF with a cut-off of 10)*

- Race/ethnicity (non-Hispanic Black, non-Hispanic White, Hispanic, non-Hispanic Other)
  - **Knowledge=decision aid + site + race/ethnciity + DA#Race/ethnicity**
  - **Decisional conflict= decision aid + site + race/ethnciity + DA#Race/ethnicity**
- Age (categorized for this analysis: <25, 25+)
  - **Knowledge= decision aid + site + age + DA#age**
- Completed Decision Aid in-person or virtual
- Recruitment Site (California, Pennsylvania, Tennessee)
- Language of the consent form (English vs Spanish)
- Education level (HS or less including GED vs. any post-high school or more)
- Provider counseling/consent form signed at T1
  - Provider sterilization counseling at baseline (before this pregnancy, during this pregnancy)

- **Participant Satisfaction with Current Contraceptive Method(s) at Time 3:** Compared to women who receive usual care alone, women randomized to the decision aid arm will report greater satisfaction with their current contraceptive method(s) at Time 3

- **Desire for sterilization:** variable will be used to assess baseline differences (pre-decision aid for intervention group, T1 for control), changes from baseline to T1 for intervention groups, and differences between post-decision aid for intervention group vs T1 for control group.

- To test exploratory hypotheses, we will first use linear regression (using the continuous measure 1-5 where higher score indicates higher desire for sterilization) to test intervention effects (pre-intervention baseline vs post-intervention T1; post-intervention vs T1 control), controlling for study site.
- We will also use ordinal regression (using the recoded 3, 4, and 5 values where higher score indicates higher strength of desire but not for/against sterilization) to test intervention effects controlling for study site.

- **Participant Knowledge about Tubal Sterilization at Time 2:** Compared to women who receive usual care alone, women randomized to the decision aid arm will have greater knowledge about sterilization and alternative options at T2.

- ***Sensitivity Analyses:*** We will run sensitivity analyses to test robustness of the intervention effects after adjusting for differences in:
  - Provider sterilization counseling between T1 and T2 (“since our last meeting”)
  - Provider contraceptive counseling between T1 and T2 (“since our last meeting”)
  - Medicaid consent signed between T1 and T2 (“since our last meeting”)
  - Provider sterilization and/or Medicaid consent signed between T1 and T2 (“since our last meeting”)
- **Participant Decisional Conflict in Postpartum Contraceptive Choice at Time 2:** Compared to women who receive usual care alone, women randomized to the decision aid arm will have lower decisional conflict in postpartum contraceptive choice at Time 2
- ***Sensitivity Analyses:*** We will run sensitivity analyses to test robustness of the intervention effects after adjusting for differences in:
  - Provider sterilization counseling between T1 and T2 (“since our last meeting”)
  - Provider contraceptive counseling between T1 and T2 (“since our last meeting”)
  - Medicaid consent signed between T1 and T2 (“since our last meeting”)
  - Provider sterilization and/or Medicaid consent signed between T1 and T2 (“since our last meeting”)
- **Contraceptive Method Selected at Time 2:** Compared to women who receive usual care alone, women randomized to the decision aid arm will be less likely to select sterilization at T2 and more likely to select an alternative method
- **Contraceptive Method(s) Used at Time 3:** Compared to women who receive usual care alone, women randomized to the decision aid arm will be less likely to select sterilization at T3 and more likely to select an alternative method
- **Ease in Contraceptive Decision Making at Time 1:** Compared to women who receive usual care alone, women randomized to the decision aid arm will report greater ease in contraceptive decision making at Time 1
- **Ease in Contraceptive Decision Making at Time 2:** Compared to women who receive usual care alone, women randomized to the decision aid arm will report greater ease in contraceptive decision making at Time 2
- **Certainty about Tubal Sterilization Decision at Time 1:** Compared to women who receive usual care alone, women randomized to the decision aid arm will report a) greater certainty about tubal sterilization decision at Time 1 and b) greater certainty in general, regardless of whether that’s for or against tubal sterilization
  - Multinomial regression (certain about not getting it vs. uncertain vs. certain about getting it) will be used to test intervention effects controlling for study site
  - Linear regression will be used (5-10, uncertain to certain) to test intervention effects controlling for study site
  - Logistic regression will be used (uncertain vs certain) to test intervention effects controlling for study site
- **Certainty about Tubal Sterilization Decision at Time 2:** Compared to women who receive usual care alone, women randomized to the decision aid arm will report a) greater certainty about tubal sterilization decision at Time 2 and b) greater certainty in general, regardless of whether that’s for or against tubal sterilization
  - Multinomial regression (certain about not getting it vs. uncertain vs. certain about getting it) will be used to test intervention effects controlling for study site
  - Linear regression will be used (5-10, uncertain to certain) to test intervention effects controlling for study site
  - Logistic regression will be used (uncertain vs certain) to test intervention effects controlling for study site
- **Participant Confidence in Contraceptive Method Selection at Time 3:** Compared to women who receive usual care alone, women randomized to the decision aid arm will report greater confidence that their current contraceptive method(s) is “right for them” at Time 3
- **Subsequent Pregnancies Since Delivery at Time 3:** Compared to women who receive usual care alone, women randomized to the decision aid arm will report lower likelihood of having a subsequent pregnancy at Time 3

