## **Exploratory Analyses in Specific Subset(s) of the Sample**

*\*Note: these analyses on specific subsets of the sample no longer rely on the randomization process. Each of the analyses below will need to assess for potential confounding factors and control for those factors in addition to study site:*

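### The Dobbs outcome models adjust calendar date for study site only, so a change in who enrolled could be read as an effect of the decision

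*Combined protocol and SAP*

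**What the plan says.** The block is in the combined protocol and SAP, under Exploratory Hypotheses. It defines three codings of date around the leak and the ruling, and asks "How has it affected our outcomes of interest". It then lists outcomes from baseline to T3, for example "Decisional conflict about contraceptive method selection at T1 predicted by date". The three-level coding is said to be useful because it "would measure effect of the leaked news and then effect of the full impact". On covariates, the text says only that "regression analyses are adjusted for study site", and it adds a date-by-state interaction for every outcome.

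The same block has a separate question on recruitment, with two items: "More interest in joining study" and "Differences in recruitment across gravida and parity".

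Two other places deal with confounding. The baseline-covariate sensitivity analyses for the primary and secondary outcomes concern imbalance between the two arms. The note that opens Exploratory Analyses in Specific Subset(s) of the Sample says: "Each of the analyses below will need to assess for potential confounding factors and control for those factors in addition to study site". It governs the three subset analyses that follow it. The Dobbs block comes before it and is not among them.

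**The concern.** The wording is causal, but the model tests something else: whether the mean outcome among enrolled women is the same before and after the cut, within site. For T1 outcomes, the women on either side of the cut are largely different women. Eligibility requires that a woman is contemplating sterilization, so anything that changes who contemplates it also changes who can enrol, on a trait close to the outcomes. Gravida and parity are collected at baseline and named as possible recruitment changes, yet they are not used.

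Calendar time also carries other changes, such as the COVID-19 recruitment redesign and differing in-person and remote procedures. These load on the date coefficient too. At stake is whether a 97.5% interval that excludes no difference is presented as Dobbs changing women's decisions, when the sample may simply have changed.

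**Working it through.** **The plan's own figures.** The plan gives no number for the Dobbs analyses. Its sample size reproduces: 2 × (2.2414 + 0.8416)² / 0.36² = 146.7, so 147 per arm, and 147 / 0.85 = 172.9, so 173, against 175 stated. That calculation concerns the randomised comparison. Only N = 350 and the two-sided 0.025 level carry over.

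**Assumptions.** The documents give no period split, case-mix shift or covariate-outcome correlation. I assume 60% of women before the cut (210) and 40% after (140), no true period effect, a baseline factor that moves by s SD after the cut, and correlation r between that factor and the outcome.

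**Formula.** Spurious difference b = s × r (in SD). SE = √(1/210 + 1/140) = 0.1091. False-positive rate = P(Z > 2.2414 − b/SE) + P(Z < −2.2414 − b/SE).

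Worked case: s = 0.3, r = 0.3 gives b = 0.09 and b/SE = 0.825. The rate is P(Z > 1.416) + P(Z < −3.066) = 0.078 + 0.001 = 7.9%.

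| s (SD) | r | b (SD) | Formula | Simulation, 3,000 runs |
|---|---|---|---|---|
| 0.2 | 0.2 | 0.04 | 3.5% | 3.4% |
| 0.2 | 0.3 | 0.06 | 4.8% | 4.1% |
| 0.3 | 0.3 | 0.09 | 7.9% | 7.9% |
| 0.3 | 0.4 | 0.12 | 12.7% | 12.7% |
| 0.5 | 0.3 | 0.15 | 19% | 20% |
| 0.5 | 0.4 | 0.20 | 34% | 33% |

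The gap in the second row is within simulation error: √(0.048 × 0.952 / 3000) = 0.4 points. With the shifted factor in the model, the simulated rate is 2.4 to 3.1%.

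**Attrition.** For T2 and T3 outcomes with 15% lost, N = 350 × 0.85 = 297.5. Then SE = √(1/178.5 + 1/119) = 0.118, and the worked case falls from 7.9% to about 7%.

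**Binary outcome** (method selected or used). The spurious difference is the change in the share of higher-parity women times the gap in outcome probability between parity groups. With a 50/50 split: 10 points × 10 points = 1 point, rate 2.8%; 20 × 20 = 4 points, 6.9%; 30 × 30 = 9 points, 29%. With a 75/25 split the extremes are 2.7% and 22%.

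**Simulation with site in the model** (continuous outcome, three sites, 50/50 split, 2,000 runs). A 20-point rise in the higher-parity share with a 0.4 SD outcome gap gives 0.08 SD and 5.6% rejection; adding the covariate gives 0.00 SD and 1.9%. A 30-point rise with a 0.6 SD gap gives 0.18 SD and 26.6%; adding it gives 0.00 SD and 2.3%. With no shift, both models stay near nominal (2.3% and 1.9%).

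**Drift.** With uniform accrual and a linear drift of D SD over recruitment, the two period means differ by D/2 wherever the cut falls. For cuts at 50 to 75% of accrual, the main date effect rejects in about 8 to 10% (D = 0.2), 15 to 20% (0.3) and 41 to 54% (0.5). If all sites share the drift and a similar accrual timetable, each state's before/after difference contains the same D/2, which cancels in the date-by-state contrast.

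**The case against.** The strongest points on the other side are these.

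- *The analyses are exploratory.* This is true, and it limits the consequence. It does not change what the date coefficient measures.
- *The plan will look at recruitment by gravida and parity anyway.* A shift on those two factors would be visible beside the outcome results, which helps a reader. It does not remove the shift from the estimates.
- *The date-by-state interaction is a partial safeguard.* This stands for drift common to the states. It does not stand for shifts or drift that differ by state, and it does not protect the main date effect.
- *The sizes are assumed.* This stands in full. At a 0.2 SD shift the rate is close to nominal, and the large figures need a 0.5 SD shift or drift, which exceeds the 0.36 and 0.46 SD effects used to size the trial.
- *A change in composition is part of what Dobbs did.* Possibly, but the plan poses recruitment and outcomes as separate questions, and a site-only model cannot separate them.

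A reader might infer that the plan expects the case mix to shift. It poses this as a question, although the item on interest is worded in one direction. A reader might also take date to mean enrolment period. The plan does not say which date it means. For T1 outcomes enrolment and assessment largely coincide; at T2 and T3 a woman enrolled before the ruling may be assessed after it.

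**Conclusion.** The point holds, as a minor one. The Dobbs outcome models give a causal reading to a non-randomised calendar contrast adjusted only for site, and nothing elsewhere in the plan supplies the missing confounder control. Bias from a shift in a measured baseline factor equals the shift times its relation to the outcome. Under the assumptions shown, the false-positive rate runs from barely above 2.5% to about a third. Which applies cannot be known from the documents.

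Three stronger conclusions are not supported. The trial's main results are not in doubt, because the primary and secondary hypotheses compare randomised arms. The drift figures do not apply to the date-by-state contrast, which is biased mainly by changes that differ by state. And a date effect that survives covariate and time-trend adjustment would still not establish an effect of Dobbs, because unmeasured selection into the study, such as motivation to join, remains.

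**What to change.** In the Dobbs block under Exploratory Hypotheses:

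1. State for each outcome whether date means enrolment or assessment date.
2. Fit the outcome models and the date-by-state models with site plus a prespecified set of baseline variables already collected, including at least gravida, parity and age. Show the site-only model alongside, and tabulate baseline characteristics by period.
3. Optionally report a model with a linear calendar-time term as a sensitivity analysis. Its power for a 0.36 SD step is about 28 to 37%, against 74 to 87% without the term. It would miss a real step of that size 63 to 72% of the time, so it must not decide the wording of the conclusion.
4. Describe all results as before/after associations, without exception.

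The cost is SAP wording, a few degrees of freedom and some extra tables. No new data are needed. Adjustment removes bias from the measured factors only, which is why item 4 is needed as well as item 2.

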### **Recruitment & Screening**

#### **Recruitment**

Prior to initiation of study recruitment procedures, healthcare providers at each site will be notified about the study and informed that patients enrolled in the study may be bringing summary sheets generated by the decision aid to clinic visits to facilitate discussions about their postpartum contraceptive decisions or decision-making process. Similar language and procedures will be used to communicate with providers across all sites in advance of the study, including emails and brief presentations during staff meeting times. Of note, the decision aid will not be shown or explained in substantial detail to avoid influencing the standard of care.

Using a combination of in-person and remote methods initiated due to COVID-19), we will **recruit 350 pregnant women** with Medicaid coverage who are contemplating a postpartum sterilization. To **optimize the racial/ethnic and geographic diversity** of our sample, the study will recruit at Magee-Women's Hospital (MWH) in Pittsburgh, Pennsylvania; University of Tennessee Medical Center (UTMC) in Knoxville, TN; Zuckerberg San Francisco General Hospital (ZSFG) in San Francisco, California. All three sites serve large numbers of low-income women. At these clinical sites, we will employ **recruitment strategies** that we have previously used to successfully recruit pregnant and reproductive-aged women, including posting study flyers throughout each clinic, asking clinical staff to refer potentially eligible women, displaying on message boards and hospital display screens, advertising on Pitt+Me (a University of Pittsburgh research registry), and Craigslist. Pre-COVID, clinic staff were stationed in each of the clinic sites to the clinic waiting rooms to facilitate enrollment during clinical visits.

The COVID-19 pandemic required recruitment redesign. To facilitate remote recruitment in the COVID era, in addition to flyers and message boards, each site will utilize electronic medical records (EMR) to identify potentially eligible persons. This process will vary by site based on local IRB and institutional guidelines for research recruitment of patients and are detailed below:

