### **Screening**

For all sites, potential participants that contact the research team or are contacted by the research team either in-person or via phone, mail, email or text message will be given a pre-screening assessment consisting of several questions to ensure they meet basic study eligibility criteria. Written or verbal consent will be obtained to conduct the pre-screening questions. During the pre-screening assessment, interested participants will be given additional study details and an opportunity to ask questions and will also be asked about their access to technology for study participation. If the potential participant is interested in participating in the study, and meets pre-screening eligibility, they will be given the option to participate in the screening, consent, and initial study procedures (randomization, baseline assessment, intervention, and T1 assessment) either in-person or remotely via telephone and/or videoconference.

Due to the evolving nature of the COVID-19 pandemic, in person procedures and safety requirements may vary by site, depending on the current conditions in each region; local restrictions and regulations will be followed. For participants that choose to participate in the study in-person at Pittsburgh and ZSFG, a telephone appointment will be scheduled 24-48 hours before their scheduled in-person healthcare clinic visit. During this telephone appointment, a full study screening and COVID-19 screening will be conducted. If the potential participant meets full study eligibility criteria, and verbally screens negative for COVID-19 symptoms and risk factors, research staff will meet the participant before or after the participant's in-person healthcare appointment at their local study site (i.e., Magee Women's Hospital or [name] for Pittsburgh participants, and Zuckerberg San Francisco General Hospital for San Francisco participants) to complete the written informed consent for enrollment and the Baseline and T1 interviews.

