|--------------------------------------------------------------|----------------------------------------------------------------------------------------------------------------------------------------------------------|------------------------------------------------------------------------|----------------------------|---------------------------------------------------------------------------------------------------------------------------------------|
| Clinic patient schedules                                     | EMR database                                                                                                                                             | Review clinic schedules to screen for potentially eligible patients    | Weekly or biweekly         |                                                                                                                                       |
| Patient contact information                                  | EMR database                                                                                                                                             | After applying eligibility criteria, store on REDCap & site hard drive | Each contact with patient  |                                                                                                                                       |
| Consent forms                                                | Verbal Consents are stored in research assistant's laptop. Written Consents are stored in a study binder behind two locks accessible to only study staff | Save or scan and upload to REDCap & site-specific hard drive           | During study enrollment    | Verbal Consents: Provide participant with blank copy (if possible)
Written Consents: Provide copy of signed consent to participant |
| Decision aid user data                                       | WordPress & Google Analytics                                                                                                                             |                                                                        |                            | Only unique user IDs will be stored                                                                                                   |

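### The pre/post-Dobbs comparisons adjust only for site, so an earlier COVID redesign of recruitment, or a pause in it, could be read as a Dobbs effect

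*Combined protocol and SAP*

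**What the plan says.** The Dobbs block under Exploratory Hypotheses asks about "SCOTUS decision impact recruitment" and then how the decision has affected the outcomes of interest. The recruitment part, under "Recruitment changes pre- and post-Dobbs", lists "More interest in joining study" and differences by gravidity and parity. The outcome part uses date to predict T1 decisional conflict, and ease, certainty and method at several visits; baseline desire for sterilization is also listed. The cuts are 1 May 2022 (the leak) and 24 June 2022 (the ruling), separately or as a three-level variable. Models adjust for site and add a date-by-state interaction for every outcome. Interest is given no definition or denominator.

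On how women were found, the Recruitment section says "Pre-COVID, clinic staff were stationed in each of the clinic sites to the clinic waiting rooms to facilitate enrollment during clinical visits". It then says "The COVID-19 pandemic required recruitment redesign" and describes identification from electronic medical records, by a different route at each site. The redesign has no calendar date. The recruitment row of Timeline of Study Activities is marked for COVID delays under Year 2 (1 May 2020 to 30 April 2021).

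No variable table lists recruitment channel or number contacted. Mode of delivering the decision aid is a covariate, described as "noted by research assistant at UT site, where virtual and in-person recruitment is being used".

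**The concern.** A before/after comparison attributes to the event whatever else differed between the periods. Here the way women were reached changed within sites during the study. Any enrolment under the waiting-room approach that the redesign replaced, and the Year 2 delays, would fall on the pre-Dobbs side of either cut. Adjusting for site removes stable differences between sites, not a change over time inside one. The date-by-state term does not help either: with three sites in three states, state is the same factor as site, so the term only lets the before/after gap differ by site.

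Two kinds of result are exposed. A rise in interest could reflect more women contacted per month, or the end of a pause. A shift in gravidity, parity, baseline desire or T1 outcomes could reflect a different kind of woman being reached. Either could be reported as the effect of a Supreme Court decision, a conclusion that would draw attention despite its exploratory label.

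**Working it through.** **The plan's own figure.** None is given for the Dobbs analyses. The only design figure is the main sample size, which reproduces: for d = 0.36, two-sided alpha 0.025 and 80% power, n = 2 × (2.241 + 0.842)² / 0.36² ≈ 147 per arm, and 147/0.85 ≈ 173 against the stated 175. Below, the total of 350 and the 97.5% interval come from the plan; every other input is an assumption.

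**1. Order of events.** The waiting-room approach is labelled pre-COVID, and the year marked for delays ends on 30 April 2021. The first Dobbs cut is 1 May 2022, a year later. Both documented disturbances therefore sit in the pre-Dobbs window.

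**2. A pause.** If a fraction f of the pre-Dobbs window had no recruitment and the rate was otherwise constant, the apparent post/pre enrolment-rate ratio is 1/(1 − f): 1.11 for f = 0.10, 1.33 for f = 0.25 and 2.0 for f = 0.50, with interest unchanged.

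**3. A change in contact volume.** Let uptake per woman contacted stay constant and contacts per month rise r-fold after the cut, with a share t of recruitment time before it. Then pre = 350t/(t + (1 − t)r), post = 350 − pre, and the log rate ratio ln r has SE √(1/pre + 1/post). For t = 0.5 and r = 1.5: pre = 140, post = 210, SE = 0.109, and 0.405/0.109 = 3.72. The 97.5% interval excludes 1 with probability Φ(3.72 − 2.241) ≈ 0.93. Over t = 0.3 to 0.7 the probability is 34–43% for r = 1.25, 82–93% for r = 1.5 and nearly 100% for r = 2. With no change in contacts it is 2.5%.

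**4. A change in who is reached.** Let the old channel supply a share s of pre-Dobbs women and none later, and let mean parity differ by δ SD between channels. The spurious difference is sδ, with SE √(1/n₁ + 1/n₂), and the rejection probability is Φ(x − 2.241) + Φ(−x − 2.241), where x = sδ/SE. The SE is 0.107 for a 175/175 split and 0.124 for 263/87.

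| s | δ | 175/175 | 263/87 |
|---|---|---|---|
| 0 | any | 2.5% | 2.5% |
| 0.10 | 0.3 | 3% | 3% |
| 0.20 | 0.5 | 10% | 8% |
| 0.32 | 0.5 | 23% | 17% |
| 0.32 | 0.8 | 56% | 43% |

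The share 0.32 is Year 1 as a fraction of the time from 1 May 2019 to the ruling (366/1150 days), so it presumes even accrual from the first day. Even accrual does not sit with a 175/175 split. The 263/87 column is more coherent with it, since 87/263 × 1150 ≈ 380 days, about 12.5 months of later recruitment. Nor is 0.32 a bound: start-up time would lower it and the Year 2 delays could raise it.

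**The case against.** The strongest reply is that nothing is documented to have changed at the cut dates. The only redesign on record is tied to COVID and undated. The record-based methods are written as current in a document whose web references were accessed in August 2022, after both cuts, so they may be identical on either side. That stands. A reader might infer that a change in outreach will be read as a Dobbs effect; the documents support only that it could be, to the extent that women enrolled before the redesign or recruitment was paused.

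Other parts also stand:

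- A reader might infer that in-person recruitment ended before Dobbs. The Knoxville site may still approach women in clinic, and flyers and message boards continued alongside the records search.
- The Screening statement that "in person procedures and safety requirements may vary by site, depending on the current conditions in each region" concerns how visits are conducted for women already pre-screened. It is not evidence that the way women were found kept changing.
- A reader might infer that interest will be measured by raw enrolment counts. The plan does not say so; the term is undefined. Screening data are held in REDCap, and the Pittsburgh site works from lists of everyone mailed.
- In the three-level coding, the contrast between the middle and last periods lies wholly after the year marked for delays, so the waiting-room approach should not confound it.
- Recruitment channel may be unrecoverable for women already enrolled.

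What does not stand is that the exploratory label or the date-by-state term settles the matter. The question remains causal, and neither separates outreach from the ruling.

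**Conclusion.** The point holds in a limited form. The plan asks a causal question of a before/after contrast, adjusts only for site, and places no restriction on a pre-Dobbs window that can include recruitment under superseded methods and a period of delay. The likely bias cannot be stated, because the documents give no pre-redesign enrolment, pause length or contact volume. The figures above show only that moderate changes would be enough to produce a false finding. If no one enrolled before the redesign, the composition bias from the old channel is zero, and what remains is a possible pause or change in contact volume.

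Importance is low. The analyses are exploratory, and the randomised primary and secondary comparisons do not depend on them.

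**What to change.** Under the Dobbs heading in Exploratory Hypotheses:

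1. Run the Dobbs comparisons, at least as the main sensitivity analysis, with the pre-Dobbs period limited within each site to months of active recruitment after that site adopted its record-based procedures. State those dates by site.
2. Where site lists, REDCap screening records or the work listed under Data Management as "Review clinic schedules to screen for potentially eligible patients" allow, analyse interest as women interested or eligible divided by women listed, contacted or screened, by site and month. Where they do not, report enrolment counts descriptively.
3. Add in-person or remote mode to the models where it was recorded, and describe date effects as associations.

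The cost is wording, a tabulation where the records permit one, and the loss of some early women, with slightly wider intervals. The randomised comparisons do not change.
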